## **6.2 Study visits**

The study procedures are in detail mentioned below. We refer to the chapters 9.1. - 9.19

## **7 SUBJECT SELECTION AND WITHDRAWAL**

### **7.1 Inclusion Criteria**

HCV-HIV co-infected SHCS participants with chronic HCV-genotype 1 infection and documented previous null-response (NR) or partial-response (paR) to standard therapy with SOC and in urgent need of treatment (i.e. METAVIR fibrosis score  $\geq 2$  or ISHAK fibrosis score  $\geq 4$  or fibroscan stiffness  $\geq 9.5\text{kPa}$ ) will be included. As cut-offs for the fibroscan we used the ones proposed in a recent review by Castera et al (19). NR is defined as less than 2 log10 IU/ml decrease in HCV RNA level from baseline at 12 weeks. paR is defined as more than 2 log10 IU/ml decrease in HCV-RNA level from baseline at 12 weeks of therapy but detectable HCV-RNA at weeks 12 and 24.

Subjects will undergo an informed consent process in accordance with GCP. To qualify for the study, subjects must meet all inclusion and none of the exclusion criteria

#### Inclusion criteria:

- Male and Female patients  $\geq 18$  years
- HIV-HCV co-infection
- HCV Genotype 1 infection
- At least one liver biopsy since diagnosis of HCV-infection
- Fibrosis score METAVIR  $\geq 2$  documented by biopsy OR a stiffness  $\geq 7.0\text{kPa}$  documented by fibroscan during the previous 12 months.
- Documented previous null-response or partial-response to SOC
- Signed Informed Consent after being informed

### **7.2 Exclusion Criteria**

The presence of any one of the following exclusion criteria will lead to exclusion of the subject:

#### Exclusion criteria:

- contraindications to the study drug under study, e.g. known hypersensitivity or allergy to any ingredient of the study drug,
- women who are pregnant or breast feeding,
- intention to become pregnant during the course of the study,
- lack of safe contraception, defined as:  
Female subjects of childbearing potential, not using and not willing to continue using a medically reliable method of contraception for the entire study duration, such as oral, injectable, or implantable contraceptives, or intrauterine contraceptive devices,

or who are not using any other method considered sufficiently reliable by the investigator in individual cases.

Please note that female subjects who are surgically sterilized/hysterectomized or post-menopausal for longer than 2 years are not considered as being of child bearing potential.

- Male patients who do not agree to abstain from intercourse or who do not use a condom
- other clinically significant concomitant unstable disease states (e.g., renal failure, unstable cardiovascular disease),
- known or suspected non-compliance, drug or alcohol abuse,
- inability to follow the procedures of the study, e.g. due to language problems, psychological disorders, dementia, etc. of the subject,
- participation in another study with investigational drug within the 30 days preceding and during the present study,
- previous enrolment into the current study,
- enrolment of the investigator, his/her family members, employees and other dependent persons
- Patients in need of ART with HIV virological failure ( $\geq 400$  copies/ml) in the last 3 months
- Any other condition that, in the opinion of the Investigator, may jeopardize the study conduct according to the protocol.

### **7.3 Subject Recruitment and Screening**

Eligible patients were selected by a review of the SHCS database (Download April 2012) using following criteria: i) HCV infection, ii) HCV genotype 1, iii) previous treatment with PR, iv) detectable HCV viral load after treatment. 80 potential eligible patients have been identified. The principal investigators of each study site (Basel, Berne, Geneva, Lausanne, Lugano, St. Gallen, and Zurich) will check the charts of their patients regarding meeting the inclusion/exclusion criteria. In the SHCS center Zurich 24 of the selected 80 patients are treated. We checked the electronic charts of these 24 patients and found 7 patients (~25%) meeting the definitive main inclusion criteria (e.g. METAVIR fibrosis score  $\geq 2$ , previous NR or pR). Accordingly we used the 25% rate for every center to estimate the minimal number of individuals who can potentially be included in this study (Tab.1).

**Table 1:** Minimal estimated number of individuals potentially eligible for therapy with Silibinin in the SHCS at present

| Centers | Number of patients |
|----------------|---------------------------|
| Basel          | 3                         |
| Berne          | 4                         |
| Geneva         | 3                         |
| Lausanne       | 2                         |
| Lugano         | 1                         |
| St. Gallen     | 2                         |
| Zurich         | 5                         |
| TOTAL   | 20                 |

The study participants will receive no payment as compensation for time and effort. Since the triple therapy is standard of care, the costs of PR and telaprevir are covered by the patients insurance.

#### **7.4 Early Withdrawal of Subjects**

The subject has to be withdrawn from the study prior the expected completion if there is a failure of the subject to adhere to protocol requirements.

Any subjects experiencing a serious adverse event felt to be related to study drug should be withdrawn from the study. Subjects will be withdrawn if they require hospitalization for addiction treatment. Any subject withdrawing their consent to participate in the study will be withdrawn from the study. Subjects discontinued from the clinical trial will be scheduled for a final evaluation and given appropriate treatment referrals. Subjects withdrawn may be replaced, at the discretion of the principal investigator.

Subjects will be informed at the consent session that treatment may be discontinued due to:

- The subject withdraws his/her informed consent to participate in the study
- Intolerable side effects
- Significantly abnormal laboratory values confirmed with a repeat testing
- Clinical deterioration for any reason or any clinical status that necessitates hospital admission
- Lost to follow up
- Protocol Violation

Reasons why subjects are discontinued from the clinical trial will be documented on the Study Termination Form, along with any referrals that are made. A final safety evaluation will be conducted as soon as possible on all treated subjects who are discontinued. This will include study-required laboratory testing, physical examination, and urine pregnancy test (women only).

## **7.5 Early Termination of Study**

The Sponsor may terminate the study prematurely according to certain circumstances:

- insufficient patient recruitment,
- when the safety or benefit of the subjects is doubtful or at risk, respectively,
- alterations in accepted clinical practice that make the continuation of a clinical trial unwise

## 8 TREATMENTS

### 8.1 Treatments to be administered

iSIL is administered in its esterified modification silibinin-C-2, 3-dihydrogen succinate disodium salt as Legalon® SIL. iSIL is administered intravenously at the first day during 4 hours and, if tolerated, from the second day during 2 hours and, if tolerated, from the third day during 1 hour. The dosage is 20mg/kg once daily for 14 days. The preparation of iSIL is done by the study-nurse.

#### Preparation of the Legalon® SIL solution:

- 1) The patient's body weight (in kilogram) is multiplied by a factor 20 (corresponding to the administered dose of 20mg/kg) obtaining the milligrams to be infused (e.g. 100 kg x 20 mg/kg = 2000 mg).
- 2) The calculated number of milligrams are divided through 350 (corresponding to the number of milligrams of silibinin contained in 1 vial Legalon® SIL). The result indicates the number of vials Legalon required to be diluted.
- 3) For every Legalon® SIL vial a syringe with 35ml sodium chloride 0.9% (NaCl 0.9%) is drawn up from a single infusion bottle of NaCl 0.9% and are injected in every single vial Legalon. Every vial contains now a solution of 350mg Legalon® SIL with a solution concentration of 10 mg/ml.
- 4) The total ml of the Legalon® SIL solution (10 mg/ml) will be calculated, dividing the milligrams obtained at point 1 per 10 (e.g. 2000mg / 10mg/ml = 200ml).
- 5) The total millilitres of the Legalon® SIL-NaCl 0.9% solution will be infused to the patients with a constant flow.
- 6) The final solution will be put into an infusion bag that is to be identified with a tear-off label supplied by RPH.

No more than 6 hours (below 30°C) should elapse once the Legalon®SIL-NaCl 0.9% solution is prepared until the end of the administration to the patient. The Legalon® SIL-NaCl 0.9% solution will be administered as scheduled to last about 1-4 hours with a constant flow.

### 8.2 Identity of Investigational Product(s)

Intravenous Silibinin (iSIL) is available on the market in its esterified modification silibinin-C-2, 3-dihydrogen succinate and disodium salt as Legalon® SIL. Legalon is currently authorized and marketed in Switzerland in the name of Max Zeller Söhne AG, licensee of Madaus GmbH a company of the Rottapharm| Madaus Group (RPH). Legalon® SIL is authorized since the mid-1980 for the treatment of hepatic intoxication with *Amanita phalloides* mushrooms in some EU Member states (e.g. in Germany since 18.04.1984). In Austria, Legalon® SIL is approved since December 2010 for the indication "Concurrent medication for patients with chronic hepatitis C who do not respond (sufficiently) to standard therapy with pegIFN / ribavirin (non-responders)". In Switzerland, Legalon® SIL has not yet been approved for treatment of chronic HCV.

### **8.3 Method of Assigning Subjects to Treatment Groups**

There is only one treatment group with Legalon® SIL, so no randomization or stratification methods will be implemented in this trial.

See section 4.6 for details.

### **8.4 Treatment Compliance**

Since the study medication (iSIL) is administered by intravenous route surveyed by the study nurse every day in the outpatient unit, the adherence should be warranted.

The patient compliance will be evaluated counting the related labels attached on the drug inventory/dispensing record and the unused boxes remaining at the trial site.

The site will be provided with a set of tear off labels; when the study medication is prepared in the site/Pharmacy, the label will be stuck on the drip/bag; before treatment administration the tear-off part of the label applied on the bag will be removed by the investigator and it will be stuck on the drug inventory/dispensing record.

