### **8.6 Packaging, Labelling and Supply**

Legalon® SIL packages will be provided to the site as pre-packaged commercially available products (re-labelled as appropriate for the clinical trial). Each carton box of Legalon® SIL contains 4 vials. One Legalon® SIL vial contains 350 mg of silibinin (315 mg according HPLC determination) corresponding to 528.5 mg silibinin-C-2 ',3-dihydrogensuccinate disodium salt (corresponding to 476 mg of mono dihydrogensuccinate sodium salts determined by HPLC method).

All packaging and labeling operations will be performed by RPH according to GMP and GCP requirements.

The test drug will be supplied as a sterile, endotoxin-free lyophilized powder for intravenous infusion in amber glass vials, packed in boxes containing four vials each.

Both vials and boxes will be labeled in English and in local language with at least the following information:

- Protocol/ Study No.
- Batch No.
- Pharmaceutical form, Dosage, Route of administration
- Sponsor Name
- Investigator Name, address and telephone number
- Storage instructions

- Expiry date
- Directions for use
- "For clinical trial use only"

Sample labels will be filed in the Trial Master File (TMF) by the Sponsor.

RPH will provide the Study drugs to each site together with the relevant documentation. The Legalon® SIL shipments will be performed by an authorised courier that will ensure continuous monitoring of the shipment temperature. The temperature under 25°C should be maintained for transport. Records of temperature measures, throughout the whole shipment period, will be provided by the courier and filed in the appropriate Trial Master File section and a copy in the Investigator's File.

After reception the Site staff must complete and return to RPH the IMP Supply Shipping/Receipt Form, verifying the receipt and integrity of the test drug. RPH will retain reference samples of the test drug.

Responsibility for Investigational Product(s) accountability at the trial site rests with the Principal Investigator or other adequately authorized delegate under the supervision of the Principal Investigator. The Site study staff should maintain records of IMP delivery, inventory at the site, use by each patient, and return or alternative disposition for unused products.

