### **11.3 Specification of Source Documents**

In addition to the medical chart of the patients and the laboratory reports, the following documents are considered source data, including but not limited to:

- SAE worksheets
- Nurse records, records of clinical coordinators, and
- Medical records from other department(s), or other hospital(s), or discharge letters and correspondence with other departments/hospitals, if subject visited any during the study period and the post study period.

Source data must be available at the site to document the existence of the study subjects and substantiate the integrity of study data collected. Source data must include the original documents relating to the study, as well as the medical treatment and medical history of the subject.

The following information (at least but not limited to) should be included in the source documents:

- Demographic data (age, sex)
- Inclusion and Exclusion Criteria details
- Participation in study and signed and dated Informed Consent Forms
- Visit dates
- Medical history, prior concomitant medication and physical examination details
- Key efficacy and safety data (as specified in the protocol)
- AEs and concomitant medication
- Results of relevant examinations
- Laboratory printouts
- Dispensing and return of study drug details
- Reason for premature discontinuation
- Patient ID number

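### Compliance is counted from labels removed before the infusion and from unused boxes, so it measures bags prepared and not drug delivered

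*Protocol*

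**What the plan says.** Section 8.4 of the protocol gives the compliance rule: "The patient compliance will be evaluated counting the related labels attached on the drug inventory/dispensing record and the unused boxes remaining at the trial site". It also fixes when the counted label is moved: "before treatment administration the tear-off part of the label applied on the bag will be removed by the investigator". The label is therefore on the record before any drug has entered the patient.

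The quantity that compliance should track is set in section 8.1: "The dosage is 20mg/kg once daily for 14 days". The preparation steps there start from weight ("The patient's body weight (in kilogram) is multiplied by a factor 20") and convert the dose to vials ("The calculated number of milligrams are divided through 350"). Section 8.6 adds that "Each carton box of Legalon® SIL contains 4 vials".

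Other drug records exist. Section 8.6 asks for use by patient, section 8.9 for amounts dispensed to each subject and for stock received, returned or unused, and section 8.10 for a final reconciliation. All follow the drug up to preparation or back to the supplier. None asks for the volume that was infused.

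**The concern.** A compliance figure is meant to tell the reader how much of the planned treatment was received. Here the count is closed before the infusion begins, so it cannot respond to anything that happens during it. An infusion halted after a few minutes and one run to the end contribute the same single label. The second measure does not help, because the vials for that bag have been opened either way.

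Partial infusions are plausible in this trial. Section 10.6 expects feelings of heat, shivering and fever, mostly during the early infusions, and section 8.1 makes the shorter infusion times conditional on tolerance. The patients most likely to receive less than planned are those who react, and those reactions are part of the primary safety endpoint.

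At stake is whether the safety, HCV-RNA and drug-level results can be read against a known exposure. The compliance figure could read 100% in a patient who received clearly less.

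**Working it through.** **Inputs from the protocol.** 20 mg per kg, 14 infusions, 350 mg per vial and a 10 mg/ml solution (8.1); 4 vials per box (8.6); label moved before administration (8.4).

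**Assumed inputs.** The number of infusions cut short (k) and the share given on those days (f). The protocol gives neither.

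**The plan's own example.** A 100 kg patient: 100 × 20 = 2000 mg; 2000/350 = 5.71, so 6 vials are opened; 2000/10 = 200 ml. The 2000 mg and 200 ml in section 8.1 reproduce.

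**Formulas.** Label compliance = labels/14. Delivered share = (14 − k + k × f)/14.

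| Infusions cut short (k) | Share given (f) | Label compliance | Delivered share |
|---|---|---|---|
| 1 | 0.50 | 14/14 = 100% | 13.5/14 = 96.4% |
| 3 | 0.50 | 14/14 = 100% | 12.5/14 = 89.3% |
| 3 | 0.25 | 14/14 = 100% | 11.75/14 = 83.9% |
| 14 | 0.50 | 14/14 = 100% | 7/14 = 50.0% |

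**Second row for the 100 kg patient.** Planned: 14 × 2000 = 28,000 mg. Infused: 12.5 × 2000 = 25,000 mg. Vials opened: 14 × 6 = 84, or 84/4 = 21 boxes, the same as with full delivery. Both measures in 8.4 are unchanged by the missing 3000 mg.

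**Could another named record supply the amount?**
- *Accountability (8.6, 8.9, 8.10).* These give amounts dispensed, unused or returned. Nothing asks for the residual volume in a bag to be measured.
- *Visit lists (9.2 to 9.15).* Vital parameters every 15 minutes and side effects in the eCRF, but no infusion start time, stop time or volume.
- *Adverse events (10.1, 10.2).* Action taken with the product is recorded and medication errors are reportable. This can show that an infusion was stopped, but not how much had been given.
- *Sample clock times (9.17).* On days 1 and 12 a pre-dose and an end-of-infusion silibinin sample are taken, so their times roughly bracket the infusion. The other 14 − 2 = 12 infusions have no such pair.
- *Pre-dose silibinin levels.* On days 2, 4 and 8 these are drawn at two sites only. With the 3-hour half-life in section 6.1 and about 20 hours between the end of the 4-hour day 1 infusion and the next dose (assuming starts 24 hours apart), about 0.5^(20/3) ≈ 1% of the end-of-infusion level remains. That is a poor guide to dose delivered.

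**The case against.** The strongest reply is that partial infusions would not go unnoticed. A study nurse supervises each one, side effects go into the eCRF, and a reaction that leads to stopping would be an adverse event with action taken recorded. The eCRF is not shown and may already hold infusion fields. Section 12 uses compliance in no analysis, and the safety population needs only one dose. All of this stands, and it limits how serious the point is. It does not repair the rule: the compliance figure in 8.4 stays wrong for a truncated infusion, and none of these records is said to hold the amount given.

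A reader might infer more than the documents support:
- *That under-delivery could not be told from true non-response.* A stopped infusion would normally leave an adverse event entry, so the possibility could be recognised. What is missing is the amount.
- *That a truncated infusion would pass as a valid Cmax.* Cmax is sampled on days 1 and 12, when recorded sample times bracket the infusion and nominal durations are 4 hours and 1 hour. A clearly short interval would show.
- *That a wrongly calculated dose is generally hidden.* An error of one vial repeated for 14 days moves 14 vials, or 14/4 = 3.5 boxes, which a box count could reveal. Different doses made from the same number of vials can each be correct for different weights and are no evidence of error.
- *That weight is not obtained.* Weight is the first step of every preparation, and the source-data list in 11.3 is stated to be non-exhaustive. Weight and height are simply not named in the schedule, visit lists or examination descriptions, although dose and the BMI co-factor (12.1) rely on them. On its own that is missing detail.

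**Conclusion.** The point holds. The compliance rule in section 8.4 counts bags prepared, and an infusion stopped early counts as a complete dose. This follows from the timing of the label and the content of the two counts; it does not depend on how often infusions are stopped.

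The size of the error in any patient is unknown. In the illustrations the label count stays at 100% while the delivered share runs from 96.4% (one infusion halved) to 50.0% (all halved), with 89.3% for three halved. The protocol gives no expected frequency of partial infusions, and nothing here shows an effect on HCV-RNA.

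The consequence is limited but real: from the records that the protocol names, exposure to 20 mg/kg for 14 days cannot be quantified alongside the safety, HCV-RNA and drug-level results. It should be corrected, because the data can only be captured at the bedside and no later analysis plan can recover them.

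**What to change.** - In section 8.4, keep the label and box counts for drug accountability only.
- For each infusion, record in the eCRF the weight used, mg prepared, start and stop times, interruptions and ml infused.
- Define compliance as mg infused divided by mg planned. With the 10 mg/ml solution of section 8.1, mg infused = ml infused × 10.
- Report this figure with the HCV-RNA, adverse event and drug-level results.
- Name weight and height in the study schedule, since the dose and the BMI co-factor rely on them.

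The cost is a few extra eCRF fields per infusion, completed by the nurse who is already present and taking vital parameters every 15 minutes. No dose, infusion time or stopping rule changes.

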### **8.5 Prior and Concomitant Therapy**

All concomitant and/or rescue treatment(s) have to be recorded in the eCRF.

Potential and harmful interactions of concomitant drugs as required dose adjustments of co-medication have to be checked by the principal investigator during the screening visit using following drug-interaction databank: [www.hiv-druginteraction.com](http://www.hiv-druginteraction.com).

If clinically indicated, drug levels of concomitant drugs have to be measured before first administration of iSIL.

### **8.6 Packaging, Labelling and Supply**

Legalon® SIL packages will be provided to the site as pre-packaged commercially available products (re-labelled as appropriate for the clinical trial). Each carton box of Legalon® SIL contains 4 vials. One Legalon® SIL vial contains 350 mg of silibinin (315 mg according HPLC determination) corresponding to 528.5 mg silibinin-C-2 ',3-dihydrogensuccinate disodium salt (corresponding to 476 mg of mono dihydrogensuccinate sodium salts determined by HPLC method).

All packaging and labeling operations will be performed by RPH according to GMP and GCP requirements.

The test drug will be supplied as a sterile, endotoxin-free lyophilized powder for intravenous infusion in amber glass vials, packed in boxes containing four vials each.

Both vials and boxes will be labeled in English and in local language with at least the following information:

- Protocol/ Study No.
- Batch No.
- Pharmaceutical form, Dosage, Route of administration
- Sponsor Name
- Investigator Name, address and telephone number
- Storage instructions

- Expiry date
- Directions for use
- "For clinical trial use only"

Sample labels will be filed in the Trial Master File (TMF) by the Sponsor.

RPH will provide the Study drugs to each site together with the relevant documentation. The Legalon® SIL shipments will be performed by an authorised courier that will ensure continuous monitoring of the shipment temperature. The temperature under 25°C should be maintained for transport. Records of temperature measures, throughout the whole shipment period, will be provided by the courier and filed in the appropriate Trial Master File section and a copy in the Investigator's File.

After reception the Site staff must complete and return to RPH the IMP Supply Shipping/Receipt Form, verifying the receipt and integrity of the test drug. RPH will retain reference samples of the test drug.

Responsibility for Investigational Product(s) accountability at the trial site rests with the Principal Investigator or other adequately authorized delegate under the supervision of the Principal Investigator. The Site study staff should maintain records of IMP delivery, inventory at the site, use by each patient, and return or alternative disposition for unused products.

For all study medications, a numbering system in accordance with all requirements of GMP will be used. This will ensure that any dose of study medication can be identified and traced back to the original bulk ware/batch of the active ingredients.

